### Plans to promote participant retention and complete follow-up {18b}

Patents will be offered a small travel allowance to attend the 3-month follow-up outpatient visits.

By doing the 6-month and 12-month follow-up scores over the telephone, no face-to-face attendances will be required beyond 3 months. This will make it more affordable to families, and the risk of patient loss to follow-up is reduced.

More than one telephone contact number will be taken so as to assist in tracing patients if parents fail to answer their telephone or the number becomes unavailable.

### Data management {19}

Data will be electronically stored in a secure password protected database. Each PI will have their own personal login and password. PIs will be able to access, but not alter, their own data.

Only the study national lead will be able to access all the data.

After 3 months of recruitment, there will be a training event looking at early data and checking accuracy.

### Confidentiality {27}

Patients will be given a study number and all data will be held in a password protected database using their study number as their unique identifier.

### Plans for collection, laboratory evaluation and storage of biological specimens for genetic or molecular analysis in this trial/future use {33}

There will be no biological specimen taken or stored in this study. There will be no blood tests collected as part of the study.

## Statistical methods

### Statistical methods for primary and secondary outcomes {20a}

The data analysis will be conducted by a statistician who is blind to the treatment groups and has not been part of the clinical study.Analyse the primary outcome using appropriate statistical methods, such as linear mixed-effects models or generalised estimating equations, adjusting for baseline functional status and potential confounders. The means of the 12-month PROMIS UE Proxy score will be used for assessing a difference above the MCID. Range analysis, including negative outliers, will also be assessed and presented in the results.Report estimated treatment effects.Compare the incidence of complications between treatment arms using appropriate statistical tests (e.g. chi-square test, Fisher’s exact test).Calculate relative risks or odds ratios for complications between treatment arms with corresponding confidence intervals.Explore potential treatment effect modification by conducting subgroup analyses based on relevant patient characteristics (e.g. age, fracture severity).Evaluate for interaction effects between treatment assignment and subgroup variables.

Missing data handling:Assess the extent of missing data and explore reasons for missingness, particularly for outcome variables.Utilise appropriate methods for handling missing data, such as multiple imputation or sensitivity analyses, to assess the robustness of results.Over-recruit by 10% case numbers above the power calculation to mitigate for missing data.

Sensitivity analyses:Perform sensitivity analyses to examine the impact of different assumptions or analytical approaches on study results (e.g. excluding patients with incomplete follow-up, adjusting for potential confounders).We intend to analyse and present results according to ‘intention to treat’ but will also undertake and present an analysis of ‘actual treatment’.

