## Interventions

### Explanation for the choice of comparators {6b}

The two treatment modalities chosen are accepted in the literature to give excellent results, and if delivered correctly, can give a low rate of complications.

Lateral straight arm traction LSAT is a low-cost intervention which can be administered by trained orthopaedic technicians. It avoids surgery or anaesthesia but has a longer length of hospital stay.

Closed reduction and percutaneous pinning CRPP is the most popular treatment method in High Income Countries HICs. It requires an operation under general anaesthetic, with a trained T&O surgeon, and availability of a C-arm for radiographic imaging during the operation. It allows a shorter average hospital stay, with the child normally discharged from hospital within 48 h of surgery (Table 1).

**Table 1 Tab1:** Schedule of enrolment interventions and assessment

	Study period						
	Enrolment	Allocation	Post allocation				Close-out
Timepoint			Within 48 h	4 weeks	3 months	6 months	12 months
Enrolment	X						
Eligibility screen	X						
Informed consent	X						
Allocation		X					
Interventions							
Closed reduction and perc pinning			X				
Lateral straight arm traction			X				
Assessments							
Flynn’s criteria				X	X		
Complications				X	X		
PROMIS scores						X	X

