### Outcomes {12}

Primary outcome: PROMIS Parent Proxy Upper Extremity – short Form 8a version 3.0, administered to patient guardian at 12 months after injury by an independent technician using Amharic or appropriate language explanation over telephone. The technician scorer will be blinded to the type of treatment received by the child and will not be permitted to ask which treatment was received.

Secondary outcomes:PROMIS Parent proxy Upper Extremity – short form 8a v3.0 at 6 monthsPROMIS Parent Proxy Global Health 7 + 2 v3.0 score at each of 6 and 12 monthsComplications, notably nerve injury, arterial compromise, Volkmann contracture, infection, secondary intervention. Scored by surgeon assessors at 3 months post injury by face-to-face clinical review.Flynn’s criteria for elbow range of movement and carrying angle assessed clinically in person by treating surgeons at 3 months after injury.Patient satisfaction with treatment using 10-point visual analogue scale. Scored in person by patient guardian, administered by treating surgeon at 3 months after injury.Economic analysis of hospital costs. Time and motion study at two representative hospital sites assessing both LSAT and CRPP using median hospital stays.

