### Participant timeline {13}

Arrive at hospital within 72 h of injury.

Invitation to join study and informed consent process.

Treatment administered within 48 h of consent.

Discharge in plaster backslab when clinically safe as judged by treating surgeons. Minimum time for LSAT is 5 days.

Clinical outpatient review 4 weeks after injury to remove plaster and start self-mobilisation.

Clinical review 3 months after injury and discharge from clinical reviews if outcome judged satisfactory by treating surgeons.

Telephone review 6 and 12 months after injury.

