## Assignment of interventions: allocation

### Sequence generation {16a}

Randomisation will be computer generated block randomisation to ensure equal numbers over the intended sample size of 220 patients. Randomisation will be stratified according to the Gartland 2b (rotational displacement only) and Gartland 3 (total off-end displacement) fractures as these are seen to represent separate patient sub-groups.

Ensuring equal numbers of each of these two sub-groups in each treatment arm will eliminate bias based on injury severity characteristics.

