### Methods for additional analyses (e.g. subgroup analyses) {20b}

We will undertake a subgroup analysis for the two fracture patterns (Gartland 2b and Gartland 3). The randomisation is already stratified for these two slightly separate diagnoses.

The subgroup analysis will include primary and secondary outcomes using the statistical techniques described above.

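### The primary analysis adjusts for a baseline functional status that no visit measures, and leaves the Gartland randomisation stratum out of the model

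*Protocol article*

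**What the plan says.** Under Statistical methods {20a}, the primary outcome is to be analysed by suitable methods, "such as linear mixed-effects models or generalised estimating equations", "adjusting for baseline functional status and potential confounders". Baseline functional status is the only covariate named. The same section adds that the 12-month means will be compared against the clinically important difference, and it lists adjustment for confounders again under sensitivity analyses.

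The measurement schedule is given in several places:

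- **Table 1** ("Schedule of enrolment interventions and assessment"): enrolment holds only the eligibility screen and consent. Flynn's criteria and complications fall at 4 weeks and 3 months, and PROMIS at 6 and 12 months.
- **Outcomes {12}**: the primary score is "administered to patient guardian at 12 months after injury by an independent technician". The same form at 6 months is a secondary outcome.
- **Participant timeline {13}**: it ends with "Telephone review 6 and 12 months after injury" and has no functional assessment on arrival.
- **Plans for assessment and collection of outcomes {18a}**: no enrolment score and no recalled pre-injury score is described.

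On allocation, Sequence generation {16a} states: "Randomisation will be stratified according to the Gartland 2b (rotational displacement only) and Gartland 3 (total off-end displacement) fractures". In the analysis this factor returns only for subgroups: fracture severity is an example in {20a}, and the two fracture patterns are the planned subgroups in {20b}.

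**The concern.** The analysis text and the measurement schedule do not fit together. A later statistical analysis plan can choose among variables that were collected, but it cannot supply a measurement that was never taken. Recruitment began on 01/08/2024 with a planned end of 31/07/2025, and the article appeared on 23 June 2025. An enrolment score introduced at publication would have missed most children.

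A baseline score would also be of doubtful use. Children enter within 72 hours of a displaced fracture, so function at that moment reflects the injury. Pre-injury function is restricted by the exclusion of prior limb deformity or malfunction, so a recalled score would probably vary little.

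Meanwhile the one prognostic factor that the design balances on purpose, Gartland type, is not named as a covariate. What is at stake is some precision in a non-inferiority comparison with a 3.5-point margin, and a clear statement of what the model may contain.

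**Working it through.** **Step 1: is the covariate measured?**

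| Time | Functional measure scheduled |
|---|---|
| Before injury (recalled) | none |
| Enrolment / allocation | none |
| 4 weeks, 3 months | Flynn's criteria |
| 6 months | PROMIS upper extremity (secondary) |
| 12 months | PROMIS upper extremity (primary) |

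Every functional measure falls after randomisation, and the four sections listed above agree on this.

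**Step 2: the plan's sample size.** Sample size {14} gives 101 per group with a difference of 3.5, and states no SD, alpha or power. The usual formula with a true difference of zero is n per arm = 2(z₁₋α + z_power)² SD² / 3.5². With SD 10, one-sided alpha 0.05 and 80% power (all assumed), 2 × (1.645 + 0.842)² × 100 / 12.25 = 100.9, so 101. Other sets of inputs give the same 101:

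- SD 8.88, one-sided 0.025, 80% power
- SD 7.67, one-sided 0.025, 90% power
- SD 8.5, one-sided 0.05, 90% power

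The loss below is therefore shown over a range.

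**Step 3: cost of omitting the stratum.** Let R² be the share of outcome variance the stratum explains (assumed 0.05 to 0.15), k = √(1 − R²), and SE = SD × √(2/101). Stratified allocation balances the factor. The true standard error is then SE × k whether or not the factor is in the model, but a model without it reports SE.

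- Power with the stratum: Φ(3.5 / (SE × k) − z)
- Power without it: Φ((3.5 − z × SE) / (SE × k))
- Type I error without it: 1 − Φ(z / k)

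Worked case: SD 8.88, so SE = 8.88 × 0.1407 = 1.249 and 3.5/SE = 2.802, with z = 1.960.

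- R² 0.05, k 0.9747: with, Φ(2.874 − 1.960) = 82.0%; without, Φ(0.842 / 0.9747) = 80.6%.
- R² 0.10, k 0.9487: 84.0% against 81.3%.
- R² 0.15, k 0.9220: with, Φ(3.039 − 1.960) = 86.0%; without, Φ(0.842 / 0.9220) = 81.9%.

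The same formulas under other assumed inputs:

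| SD | One-sided alpha | R² 0.05: with / without | R² 0.15: with / without |
|---|---|---|---|
| 7.67 | 0.025 | 91.4 / 90.6 | 94.0 / 91.8 |
| 8.88 | 0.025 | 82.0 / 80.6 | 86.0 / 81.9 |
| 10 | 0.025 | 72.3 / 70.6 | 77.0 / 71.6 |
| 10 | 0.05 | 81.8 / 80.6 | 85.4 / 82.0 |
| 8.5 | 0.05 | 91.3 / 90.6 | 93.7 / 91.8 |

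The loss runs from 0.7 to 5.3 percentage points. Without the stratum the interval is wider by a factor of 1/k, which is 1.03 at R² 0.05 and 1.08 at R² 0.15. At a nominal 0.025, the type I error falls to 0.022 and 0.017. The error is conservative.

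**The case against.** Several points on the other side are fair.

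- **The analysis is still feasible.** A reader might infer that the primary analysis cannot be run at all. The documents do not support that. Sections {18a} and {20a} both describe a comparison of 12-month group means against 3.5 points, which needs no baseline score. One adjustment term is unsupported, not the whole analysis.
- **The 6-month score is not offered as a baseline.** A reader might fear that this score, the only earlier PROMIS value, would fill the gap. With equal SDs the adjusted effect would be D12 − ρ × D6. With an assumed ρ of 0.6 and a deficit of 3.5 at both times, it would be −3.5 + 0.6 × 3.5 = −1.4, a shift towards non-inferiority. The arithmetic is right, but no section proposes this use, and Outcomes {12} lists the score as an outcome. It justifies a sentence ruling the practice out, not a charge against the plan.
- **The standard error errs on the safe side.** A reader might take the omitted stratum as a threat to validity. It makes a false claim of non-inferiority less likely, so the cost is power only.
- **Table 1 is not exhaustive.** It omits the 3-month satisfaction scale and shows no baseline characteristics, and the eligibility section has nerve injuries documented. But the outcomes, timeline and data collection sections also contain no early functional score, and a nerve finding is not a functional status measure.
- **Covariates are often left to the analysis plan.** The unnamed confounders could include Gartland type, and a mixed model could carry site. This stands for age and site. Site is not a stated stratification factor, so neither term is owed to the design. It does not rescue a named covariate that was never scheduled.

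**Conclusion.** The contradiction holds: {20a} names a covariate for which the protocol schedules no measurement, and a recalled substitute would probably carry little information. Leaving the Gartland stratum out of the primary model is a secondary weakness. It does not bias the estimate, makes the interval about 3 to 8% too wide, and costs about 1 to 5 percentage points of power. Those figures assume that the stratum explains 5 to 15% of variance, that it is balanced, that the true difference is zero, and that 101 children per arm are analysed. If the stratum explains nothing, the loss is nil. The point should be fixed, but it does not endanger the main comparison.

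**What to change.** In Statistical methods {20a}:

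1. Delete the reference to baseline functional status.
2. State that the 12-month PROMIS upper extremity T-score is compared between arms with adjustment for the Gartland randomisation stratum (2b or 3). Age, and site as a fixed or random effect, may be added if they are named before unblinding.
3. State that no score taken after randomisation, including the 6-month PROMIS, is used as a covariate. The 6-month score may enter only as a repeated outcome in a longitudinal model.

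The cost is two or three sentences. Gartland type has to be known for each child to apply the eligibility criteria and the stratified allocation, age is needed for eligibility, and site is known. No new data collection is required.

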### Interim analyses {21b}

Since both treatment options are established and accepted options, and the LSAT method may be slower to achieve full recovery of function and therefore PROM, the study will be allowed to recruit the expected 220 patients unless a safety concern is raised by the PIs or the complication findings. Complication findings will be assessed at 3-month intervals or additionally if a concern is raised.

### Methods for additional analyses (e.g. subgroup analyses) {20b}

We will undertake a subgroup analysis for the two fracture patterns (Gartland 2b and Gartland 3). The randomisation is already stratified for these two slightly separate diagnoses.

The subgroup analysis will include primary and secondary outcomes using the statistical techniques described above.

### Methods in analysis to handle protocol non-adherence and any statistical methods to handle missing data {20c}

Investigate and report any protocol deviations or violations and assess their potential impact on study outcomes.

See also the section above relating to missing data.

Some protocol deviations are expected regarding cross over from non-operative LSAT to operative CRPP. This will be considered using the intention to treat and actual treatment analyses, and both will be presented.

Minor variations within the protocol arms will be noted and ignored as the aim is to be pragmatic and reflect normal variations between treating surgeons when using one or other of these two methods. Thus, all such patients will be included in the analysis.

### Plans to give access to the full protocol, participant level data and statistical code {31c}

Our full data would be available on request to relevant parties.

## Oversight and monitoring

### Composition of the coordinating centre and trial steering committee {5 d}

Our oversight team includes a Project Manager, Financial Manager, International Medical Director, National Society President, National Surgeon Manager, and the PIs.

Progress meetings, problem solving, and interim reporting and data checks will be undertaken every 3 months either in person or online.

### Composition of the data monitoring committee, its role and reporting structure {21a}

Data monitoring will be undertaken by the national Surgeon Director with reference to the International Medical Director.

Whilst the International Medical Director is a consultant for the funding body, AO Alliance Foundation, this organisation is a developmental NGO without commercial bonding and is therefore not considered to be a conflict of interest.

### Adverse event reporting and harms {22}

Assessment of complications—iatrogenic and other—forms one of the secondary outcomes of the study and will be related at 4 weeks, and 3 months. Since both treatment methods are recognised as standards of care and are in current use in Ethiopia, we consider that this is a low-risk study for adverse events. The national surgeon lead and the international Medical Director will be responsible for assessing adverse events and suspending or stopping the trial if concerns arise.

Interventions made by the oversight team will be reported in all publications.

### Frequency and plans for auditing trial conduct {23}

No independent audit is planned.

### Plans for communicating important protocol amendments to relevant parties (e.g. trial participants, ethical committees) {25}

The ethical committee and the trial registration body will be informed of any protocol amendments. The PIs will be informed and will cascade to their teams.

### Dissemination plans {31a}

We plan to disseminate results by local, national and international presentations and one or more publications in a relevant international peer-reviewed journal.

## Discussion

The study is set up with 8 participating sites, but the Trial management team will invite further sites to participate if recruitment is slow, such that the anticipated recruitment period will exceed 12 months.

### Trial status

This is protocol v1.

Recruitment started 01/08/2024.

Anticipated recruitment is 12 months ending 31/07/2025.

## Data Availability

The complete dataset will be handled by the National lead ([name]) and the International Medical Director ([name]). Hospital PIs will have access to and rights over their own hospital data.

## Abbreviations

LSAT: Lateral straight arm traction
CRPP: Closed reduction and percutaneous pinning
NGO: Non-Governmental Organisation
LMIC: Low- and middle-income country
HIC: High-income country
AO Alliance: Arbeitsgermeinshaft fur Osteosynthesefragen Alliance
T&O: Trauma and Orthopaedics
IRB: Institutional Review Board
